**Figure 1 F1:**
[figure not shown]
**Flowchart of the study**. ^1 ^The online diary is used for monitoring blood glucose measurements. ^2 ^Feedback consistsof 1. a graphic presentation of the input 2. a dose advice for thenext 2 days or coming period 3. compliments/advice. ^3 ^Alerts are generated when there is a medical urgency: hypoglycaemia (< 2.5 mmol/l) or hyperglycaemia (FBG > 20 mmol/l). When the patient gets an alert (feedback and advice), this is also sent to the GP. ^4 ^Follow up consists of questionnaires and measurements of physical and clinical characteristics (see text: 'outcome assessment').

### Blinding

It is impossible to blind the participants and health care providers (GP and practice nurse) for the intervention. The investigators will remain blinded during the entire intervention.

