### Randomisation and treatment allocation

General practices will be randomly assigned to the intervention or control group using a computerized randomisation programme. In case a practice nurse takes care of the insulin titration (working for one or more general practices), the practice nurse will be randomised and corresponding general practice(s) will be allocated to one of the groups. It is desirable that the two groups will be similar with regard to the amount of patients in each group. For that reason we will apply stratified randomisation [34]. Clusters with one or two general practices and clusters with three or more general practices will be randomised separately. Randomisation will be performed by the manager of the website company (Curavista B.V., Geertruidenberg, the Netherlands), who is independent of the patients and their care. Patients in the intervention group will self-adjust the insulin dose supported by an internet programme and receive education before starting insulin. The control group will receive physician-driven (GP or practice nurse) adjustments, i.e. the GP or practice nurse will perform the insulin titration in his/her own manner, guided by guidelines from the Dutch College of General Practitioners.

When a patient is eligible to participate in our study the GP or practice nurse will provide a letter of invitation and an information brochure of the trial based on the assigned group. The next visit will be scheduled one week later in which the patient can give his or her informed consent to participate in the trial.

The flow of the patients is registered by the investigator (MR), according to a flow diagram recommended by the CONSORT statement and its extended version to cluster randomised trials [35,36]. Reasons for withdrawal are registered by the practice nurse or GP. Figure 1 shows the design of the study.

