### Study procedure

Approximately 62 GPs (see 'sample size calculation') will be recruited by the principle investigator (MR) and thereafter randomly assigned to the intervention group or control group. Their patients will be allocated to the assigned group.

In the present study, eligible patients will receive insulin glargine. Once-daily injection of a long-acting insulin is attractive, because of the simple dose adjustments based on fasting blood glucose values. It provides at least equivalent glycaemic control to NPH insulin but with a lower incidence of hypoglycaemia [5,25,37]. The GP is free to continue all oral agents, except for thiazolidediones [4].

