#### Intervention group

When informed consent is given, patients in the intervention group will receive individual education on diabetes in general, all aspects of insulin treatment, the use of a self-monitoring device, the importance of self-monitoring, and aspects of hypo- and hyperglycaemia. In addition, information about diabetes in general and its management is available on the trial website (provided by [38]), an online education programme developed by the University of Maastricht and the Academic Hospital Maastricht, the Netherlands). The education will be given in two sessions (with an interval of 1 or 2 weeks) by the GP or practice nurse in general practices using a standard protocol provided by the investigators. The patients will receive a manual how to use the internet programme.

The internet programme is accessible through a log-in procedure, requiring a log-in name and a password. The programme is not accessible for the control group or others without permission. In case of problems, patients can always contact their practice nurse or GP, who do have access to the online data of their patients.

Patients will start with 10 IE insulin glargine. The next day, a patient has to log-in in order to start the internet programme, that consists of an online-diary with computerized algorithms. Feedback will be given on fasting blood glucose (FBG) measurements that have to be completed in the diary. The programme will reply with an insulin dose advice when two FBG measurements (on two successive days) are inputted (+ 4 IE when FBG exceeds 10 mmol/l for 2 consecutive days; + 2 IE when FBG is between 7–10 mmol/l for 2 consecutive days; – 2 IE when FBG is between 2.5–4 mmol/l for 2 consecutive days; – 4 IE when FBG is below 2.5 mmol/l for 2 consecutive days). In case of a high or low FBG level, the programme will also respond with a feedback question, guided by the self-regulation theory. According to the patients' answer, advice will be given on the concerning item (e.g. adjustment of diet or increase of physical activity). Feedback will also be given visually in colours, tables and graphics.

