### Outcome assessment

Outcome measurements are assessed by means of self-administered web-based questionnaires (accessible with a log-in name and password provided by email for both the intervention and the control group) and physical examination at the general practices. If questionnaires are not completed within one week an email-reminder will be sent to the participants. In case of no response, a phone call to their general practice will be made by the investigator. Physical and clinical data will be obtained from the usual 3-monthly check-ups for diabetes patients in their own practice. The practice nurse or GP will record patients' diabetes duration, co-morbidity, pre-existing diabetes complications, and medication at baseline.

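### The statement that the investigators stay blinded throughout the intervention is not credible as written, given the tasks the article assigns to them

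*Protocol article*

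**What the plan says.** The Blinding section has two sentences. The first concedes that patients and practice staff are unblinded: "It is impossible to blind the participants and health care providers (GP and practice nurse) for the intervention". The second reads "The investigators will remain blinded during the entire intervention". It does not say which investigators are meant, what they are blinded to, or how the blind is kept. It is the only masking that the article claims.

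Other sections give the investigators these tasks:

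- Study procedure: the roughly 62 GPs "will be recruited by the principle investigator" and are randomised after that.
- Randomisation and treatment allocation: "The flow of the patients is registered by the investigator", and this is done "according to a flow diagram recommended by the CONSORT statement and its extended version to cluster randomised trials". The article gives the same initials here as for the principal investigator who recruits.
- Intervention group: the GP or practice nurse gives the education in two sessions "using a standard protocol provided by the investigators".
- Outcome assessment: when a participant still has not answered after an email reminder, "a phone call to their general practice will be made by the investigator".

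The allocation itself is made by someone else: "Randomisation will be performed by the manager of the website company".

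**The concern.** Blinding is claimed for a whole group, without exception, for the whole intervention period. The same group supplies material to one arm, keeps a record that is normally split by arm, and speaks with staff who know the arm. If the claim cannot hold, the trial report would credit the study with a protection that its own procedures do not support.

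Readers would rely on that claim when they judge steps in which an investigator's knowledge of the arm could matter: following up missing questionnaires, keeping the flow record, and choosing among analyses. The last of these has room to matter. The Analysis section names both t-tests and multilevel regression, gives the prognostic factors as examples, and makes the adjustment conditional on being suitable. The Discussion adds all co-medication as a possible confounder or effect modifier.

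**Working it through.** No arithmetic applies. The sample size (62 practices, 248 patients) does not use the blinding statement and is unaffected by it. The check sets each task beside the Blinding sentence and asks whether the task can be done without learning a practice's arm.

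1. **Randomisation by the website company's manager.** This keeps the investigators out of generating the sequence. It says nothing about what they learn once practices have been told their group, so it does not support a claim covering the entire intervention.

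2. **Recruiting practices.** This comes before randomisation and reveals nothing in itself. It matters only because the recruiter knows the practices by identity and, by the initials given, is also the person in step 4.

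3. **Providing the education protocol.** The education is described only under Intervention group. The Control group section has patients instructed by their GP or nurse as usual. Anyone who supplies the protocol to practices therefore knows that those practices are in the intervention arm. Writing it and leaving distribution to someone else would not reveal the arm, but the article names the investigators as providers and mentions no one else.

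4. **Registering patient flow.** A CONSORT flow diagram for a cluster trial normally shows clusters and patients by allocated group. It could be kept under coded group labels, but the article describes no coding. Here the person keeping the record has also recruited the practices.

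5. **Telephoning practices about non-responders.** The call applies to both arms and need not mention allocation. It is nevertheless direct contact during follow-up with staff whom the Blinding section calls unblinded. Allocation is by practice, or by practice nurse where the nurse titrates insulin. One disclosure therefore reveals the arm of every participant in that practice (about 4 by the sample size section), or of every practice that the nurse serves. The article does not say whether this investigator is the one in steps 2 and 4.

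6. **Tasks not counted.** The invitation letter and brochure differ by group, but the GP or nurse hands them out and no supplier is named. The supplier of the GPs' handling protocols is not named either.

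Steps 3 to 5 are three separate routes by which an investigator would, or easily could, learn allocation. None is closed by anything the article describes.

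**The case against.** The strongest reply is that no sentence says an investigator sees a practice's arm. A third party randomises, recruitment comes first, the education protocol might be distributed by others, the flow log might use codes, and a reminder call need not disclose anything. All of this is possible, and it limits what can be claimed. A reader might infer that the investigators definitely know every practice's arm and that no masking exists at all. The article does not support that. It supports a narrower statement: the claim is unqualified, the tasks work against it, and no mechanism reconciles them.

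A second reply concerns harm, and most of it stands. HbA1c is a measured value taken at practice check-ups. The other main outcomes come from self-administered web questionnaires and a patient diary. Their risk of bias comes mainly from patients who know their treatment, and blinded investigators would not remove it. A reader might also infer that chasing of questionnaires is discretionary or that investigators classify withdrawals. The article says otherwise: the reminder sequence is fixed (one week, email, then a call), and the GP or practice nurse records the reasons for withdrawal. The 15% dropout allowance is a sample size input and does not measure any effect of lost blinding.

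A third reply is that analyst masking is commonly left to an analysis plan, which is not shown here. That is fair, and its absence is not held against the article. However, an analysis plan could mask the analyst without making the Blinding sentence consistent with the other sections.

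**Conclusion.** The point holds in a limited form. The Blinding sentence is not credible as written and must be reconciled with the sections on randomisation, the intervention group and outcome assessment. The primary result is not invalidated, and no figure in the plan changes.

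The remaining exposure has three parts: contact with the practices of non-responders, the flow record, and the analysis choices left open in the Analysis section. Its size cannot be calculated from the document.

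The conclusion rests on three readings: that the investigators who provide the education protocol also learn which practices receive it, that the flow record is kept by arm in the usual way, and that no coding or intermediary exists beyond what the article describes. If the full protocol contains such a mechanism, stating it would settle the matter for the roles it covers.

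**What to change.** Replace the blanket sentence in the Blinding section with a statement by role:

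- Withdraw the claim for any investigator who supplies arm-specific material, keeps the flow record or calls practices.
- State that the data analyst works on a dataset with coded arms until the primary analysis and its covariates are final.
- Issue the call list for questionnaire non-responders without the arm. The reminder sequence already fixed under Outcome assessment can stay as it is.

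No masked classification of withdrawals is needed, because the article describes no such step by the investigators.

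The change costs a short rewording, a coded-arm dataset and a call list with one column removed. It needs no extra patients, visits or practices. The downside is a less favourable blinding statement than the present one.

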### Study procedure

Approximately 62 GPs (see 'sample size calculation') will be recruited by the principle investigator (MR) and thereafter randomly assigned to the intervention group or control group. Their patients will be allocated to the assigned group.

In the present study, eligible patients will receive insulin glargine. Once-daily injection of a long-acting insulin is attractive, because of the simple dose adjustments based on fasting blood glucose values. It provides at least equivalent glycaemic control to NPH insulin but with a lower incidence of hypoglycaemia [5,25,37]. The GP is free to continue all oral agents, except for thiazolidediones [4].

#### Intervention group

When informed consent is given, patients in the intervention group will receive individual education on diabetes in general, all aspects of insulin treatment, the use of a self-monitoring device, the importance of self-monitoring, and aspects of hypo- and hyperglycaemia. In addition, information about diabetes in general and its management is available on the trial website (provided by [38]), an online education programme developed by the University of Maastricht and the Academic Hospital Maastricht, the Netherlands). The education will be given in two sessions (with an interval of 1 or 2 weeks) by the GP or practice nurse in general practices using a standard protocol provided by the investigators. The patients will receive a manual how to use the internet programme.

The internet programme is accessible through a log-in procedure, requiring a log-in name and a password. The programme is not accessible for the control group or others without permission. In case of problems, patients can always contact their practice nurse or GP, who do have access to the online data of their patients.

Patients will start with 10 IE insulin glargine. The next day, a patient has to log-in in order to start the internet programme, that consists of an online-diary with computerized algorithms. Feedback will be given on fasting blood glucose (FBG) measurements that have to be completed in the diary. The programme will reply with an insulin dose advice when two FBG measurements (on two successive days) are inputted (+ 4 IE when FBG exceeds 10 mmol/l for 2 consecutive days; + 2 IE when FBG is between 7–10 mmol/l for 2 consecutive days; – 2 IE when FBG is between 2.5–4 mmol/l for 2 consecutive days; – 4 IE when FBG is below 2.5 mmol/l for 2 consecutive days). In case of a high or low FBG level, the programme will also respond with a feedback question, guided by the self-regulation theory. According to the patients' answer, advice will be given on the concerning item (e.g. adjustment of diet or increase of physical activity). Feedback will also be given visually in colours, tables and graphics.

The process of using the online-diary will continue until the patient has reached a normal FBG (FBG between 4.0 and 7.0 mmol/L). At that point he/she is advised to make a 5-point day-curve. Dependent on the value of one of the measured glucose values, the internet programme will automatically respond with a feedback question or will give advice to repeat the day-curve after 2 days. When a stable insulin dose is reached (all measurements are within the range of 4.0 – 9.0 mmol/L), it is advised to measure FBG once a week. When repeated day-curves (4 day-curves in approximately one week) are not within normal range, it is advised to contact the GP or practice nurse. Protocols for how to act in different situations will be provided to the GP's. If another or additional (short-acting) insulin is started, patients will not be able to use the internet programme any longer. This is also the case if the insulin dose exceeds 80 IE. If the GP or practice nurse needs extra advice, a diabetes nurse from the Diabetes Research Center can be contacted.

#### Control group

Patients in the control group will receive individual instructions with regard to insulin dose-adjustments from their GP or practice nurse as usual. The number or type of contacts might differ per practice. The titration scheme of insulin glargine will be determined by the GP or practice nurse. Because there is no strict regimen, this can also differ per practice. The patients are offered access to the information provided on the trial website and for completing the web-based questionnaires only. GPs or practice nurses can contact a diabetes nurse from the Diabetes Research Center concerning questions about the insulin therapy.

### Outcome assessment

Outcome measurements are assessed by means of self-administered web-based questionnaires (accessible with a log-in name and password provided by email for both the intervention and the control group) and physical examination at the general practices. If questionnaires are not completed within one week an email-reminder will be sent to the participants. In case of no response, a phone call to their general practice will be made by the investigator. Physical and clinical data will be obtained from the usual 3-monthly check-ups for diabetes patients in their own practice. The practice nurse or GP will record patients' diabetes duration, co-morbidity, pre-existing diabetes complications, and medication at baseline.

#### Primary outcome measure

The primary outcome measure is the difference in change in glycaemic control (HbA1c) between intervention and control group. HbA1c will be measured at baseline, 3 and 12 months. The measurement of HbA1c at 6 or 9 months will take place only if HbA1c is still above 7% at 3 respectively 6 months.

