### Sample size calculation

The sample size is calculated to detect a clinical relevant difference of 0.5% in HbA1c between groups. In the Diabetes Care System West-Friesland the standard deviation (sd) of HbA1c of the general diabetes population is 1.2% [49]. A difference (d) between the intervention and control group in changes of 0.5%, a standard deviation (sd) of 1.2%, an alpha of 0.05 (two-sided), and a power of 80%, the number of patients requested in each group is 90.

Because cluster randomisation is applied at the level of general practices, the number of patients has to be multiplied with the following formula: 1 + (k-1)ρ, in which ρ is the intercorrelation coefficient (ICC) between practices. The ICC is statistically determined to be 0.05. k is the number of patients per practice that will join the study. Based on our experience, we estimate that 4 patients per practice will make the transition to insulin treatment in one year and meet the criteria of our trial. A participation of 26 general practices is needed per group:

Furthermore, taking into account a possible dropout rate of 15%, the total number of practices needed is: 2 * 26/(1–0.15) = 62, which means that 248 patients will be required.

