### Analysis

Descriptive statistics (means ± SD or median and inter quartile range as appropriate) will be used to describe the study sample with regard to demographics and baseline (clinical) characteristics. On the basis of an intention-to-treat analysis, differences in changes between the intervention group and control group are calculated with 95% confidence intervals at 3, 6 and 12 months for both primary and secondary outcomes.

Using *t*-tests and multiple linear regression – duly adapted for the multilevel structure of the data – we will compare changes in HbA1c, number of hypoglyceamias, quality of life, treatment satisfaction, illness and insulin perceptions and confidence in diabetes self-care scores at different time intervals between the groups, with adjustment for important prognostic factors like age, diabetes duration, medication and level of education where appropriate. Separate analyses of possible effect modifiers (i.e. age, depression, previous internet use) will be performed in order to gain a better understanding as to who benefits most from the intervention.

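### The planned 6-month HbA1c comparison uses only patients still above 7% at 3 months, so it is not intention-to-treat and can be biased, mostly towards no effect

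*Protocol article*

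**What the plan says.** Under Primary outcome measure, the outcome is defined without a time point: "The primary outcome measure is the difference in change in glycaemic control (HbA1c) between intervention and control group". The same section gives the schedule. For all patients, "HbA1c will be measured at baseline, 3 and 12 months". The other two visits are conditional: "The measurement of HbA1c at 6 or 9 months will take place only if HbA1c is still above 7% at 3 respectively 6 months".

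The Analysis section opens the comparison with "On the basis of an intention-to-treat analysis, differences in changes between the intervention group and control group" and says that these "are calculated with 95% confidence intervals at 3, 6 and 12 months for both primary and secondary outcomes". HbA1c heads its list of variables to be compared. The methods are t-tests and "multiple linear regression – duly adapted for the multilevel structure of the data".

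Under Other data collection, the three-monthly physical and clinical measurements include fasting plasma glucose but not HbA1c. No other source of a 6-month HbA1c is given.

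**The concern.** Patients at or below 7% at 3 months have no planned 6-month HbA1c, so a t-test or regression of change at 6 months has to leave them out. Whether a patient is left out depends on the 3-month value of the primary outcome, which the programme is designed to lower. The remaining groups are therefore not the randomised groups. If the programme works early, fewer intervention patients than controls remain, and they are more strongly selected for poor response.

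No primary time point is named, so the 6-month difference would stand as one of three stated results for the primary outcome. It could understate a benefit. It could also suggest a small harm if an early benefit had disappeared by 6 months.

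**Working it through.** **1. The plan's own figures.** Inputs from Sample size calculation: difference 0.5, SD 1.2, two-sided alpha 0.05, power 80%, ICC 0.05, 4 patients per practice, dropout 15%.

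- n per arm = 2 × (1.960 + 0.842)² × 1.2² / 0.5² = 90.4 (stated: 90).
- Design effect = 1 + (4 - 1) × 0.05 = 1.15; 90 × 1.15 / 4 = 25.9, so 26 practices per arm.
- 2 × 26 / 0.85 = 61.2, so 62 practices and 62 × 4 = 248 patients.

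These reproduce. None of them is tied to 6 months, and nothing below changes them.

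**2. The HbA1c schedule against the planned contrasts.**

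| Month | HbA1c measured in | Between-arm contrast planned |
|---|---|---|
| 3 | everyone | yes |
| 6 | only those above 7% at 3 months | yes |
| 9 | only those above 7% at 6 months | no |
| 12 | everyone | yes |

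Only month 6 is in conflict.

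**3. Why selection shifts the contrast.** Write B, A3 and A6 for HbA1c at baseline, 3 and 6 months. With jointly normal values, within an arm:

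mean(A6 - B, given A3 > 7) = mean(A6 - B) + β × [mean(A3, given A3 > 7) - mean(A3)]

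Here β is the slope of A6 - B on A3. With equal SDs, and ignoring the entry cut at 7.0%, β = r(3,6) - r(B,3). The bias in the arm difference is β times the between-arm difference in the bracket.

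Example (assumed: control 3-month mean 7.5, intervention 7.0, SD 1.2, r(B,3) = 0.4, r(3,6) = 0.7):

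- The bracket equals SD × φ(z)/[1 - Φ(z)], with z = (7 - mean)/SD.
- Control: z = -0.417, bracket = 1.2 × 0.553 = 0.66.
- Intervention: z = 0, bracket = 1.2 × 0.798 = 0.96.
- Bias = (0.7 - 0.4) × (0.957 - 0.663) = 0.3 × 0.294 = +0.09, so a true -0.50 appears as about -0.41.

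Simulation of the same case with the entry cut gives -0.39. The formula also shows the limits. There is no bias if the arms do not differ at 3 months, because the brackets are then equal. There is little bias on unadjusted change if the two correlations are about equal.

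**4. Simulation.** Assumptions that are not in the documents: baseline mean 8.5 cut at 7.0; control 3-month mean 7.2 to 8.0; SD 0.8 to 1.2; correlations baseline/3-month 0.3 to 0.6, 3-/6-month 0.6 to 0.8, baseline/6-month 0.25 to 0.5; effect -0.50 at 3 months. Selected rows, with correlations in that order:

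| Control 3-month mean, SD | Correlations | Measured at 6 months, control / intervention | True -0.50: change / baseline-adjusted | True 0 at 6 months: change / baseline-adjusted |
|---|---|---|---|---|
| 7.2, 0.8 | 0.5, 0.8, 0.45 | 61% / 36% | -0.39 / -0.28 | 0.10 / 0.22 |
| 7.2, 1.2 | 0.4, 0.7, 0.35 | 60% / 43% | -0.38 / -0.30 | 0.12 / 0.20 |
| 7.5, 1.2 | 0.4, 0.7, 0.35 | 69% / 53% | -0.39 / -0.32 | 0.11 / 0.18 |
| 7.5, 1.2 | 0.6, 0.6, 0.5 | 71% / 55% | -0.49 / -0.40 | 0.02 / 0.11 |
| 8.0, 1.2 | 0.4, 0.7, 0.35 | 83% / 69% | -0.41 / -0.36 | 0.09 / 0.14 |

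Over all settings the measured-only difference in change is -0.38 to -0.50, or -0.28 to -0.43 if baseline-adjusted. If the effect has vanished by 6 months, it is 0.01 to 0.12, or 0.07 to 0.22, against the intervention. With no effect at either visit it is about 0.

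A second simulation under other assumptions (baseline mean 8.8, control fall 0.9, residual SD 1.0, residual correlation 0.4 to 0.8) gives -0.46 to -0.37 on change and -0.41 to -0.31 baseline-adjusted.

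**5. Recovery.** Predicting the missing 6-month values from baseline, 3-month HbA1c and arm returns about -0.50 (and about 0 under a zero effect) in these data, which were generated as linear.

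**The case against.** - **The analysis sentence may be shorthand.** It names 3, 6 and 12 months for all outcomes, yet the SF-12 and the treatment satisfaction questionnaire are collected only at baseline, 3 and 12 months. It may mean whichever visits apply to each outcome. This weakens the literal reading but does not remove it: the sentence expressly includes the primary outcome, and HbA1c does have some 6-month values to which the stated tests could be applied.
- **Missing-data handling belongs in an analysis plan that is not shown.** This holds for the details of a model. It does not cover a measurement rule, a set of time points, a population and a method that the article itself fixes and that do not fit together. The multilevel adaptation is not said to extend to repeated measures.
- **The bias is not established.** This stands in part. Its size depends on assumed correlations, and the range on unadjusted change reaches no bias at all. A reader might infer a firm attenuation of 18 to 38% from the second simulation's -0.41 to -0.31, since (0.50 - 0.41)/0.50 = 18% and (0.50 - 0.31)/0.50 = 38%. Those figures rest on adjustment for baseline HbA1c, which the Analysis section does not name, although its list of prognostic factors is open. On change, the same simulation gives 8 to 26%.
- **A repeated-measures model would settle it.** A reader might infer that, because the 7% rule depends on an observed value, such a model is simply valid. But patients at or below 7% at 3 months never have a 6-month value under the plan, so the model extrapolates to them from patients above 7%. In a check with an assumed different 3-to-6-month slope on the two sides of 7%, linear prediction gave -0.20 against a true -0.28. That check did not test a full model with 12-month data. Nor is the expected 15% dropout missing by design.

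**Conclusion.** The point holds as an inconsistency that makes the 6-month HbA1c contrast, as written, a comparison of 3-month non-responders rather than an intention-to-treat comparison. Bias follows if the programme affects HbA1c by 3 months, which the trial expects. It then runs mostly towards no effect.

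Against the 0.5 target difference, a true -0.50 would be seen as about -0.37 to -0.50 on change, an attenuation of 0 to 26% ((0.50 - 0.37)/0.50 = 26%), or about -0.28 to -0.43 if baseline-adjusted. These sizes rest on assumed means, SDs and correlations.

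A reader might infer that the trial's main HbA1c result is compromised. The document does not support that. HbA1c is planned for everyone at 3 and 12 months, the sample size is not tied to 6 months, and no text makes 6 months the primary time point. The questionnaires scheduled for 6 months are not subject to the 7% rule. This should be fixed, but it does not threaten the trial's main comparison.

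**What to change.** In the Analysis section, restrict the between-arm HbA1c contrasts to 3 and 12 months, when everyone is to be measured. This needs no modelling assumption about unmeasured 6-month values.

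If a 6-month HbA1c estimate is kept, obtain it from one longitudinal multilevel model of all HbA1c values, including month 3, for all randomised patients. Label it supportive. State that it extrapolates to patients at or below 7% at 3 months, and that missing at random remains an assumption for dropout.

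The cost is wording only: no extra measurement and no change to the 248 patients. The downside is that the 6-month HbA1c contrast is either lost or becomes model-dependent.
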